### Baseline assessments

Participants from throughout New Zealand will call Quitline seeking advice and wishing to enrol in the Quitline smoking cessation programme. A Quit advisor from Quitline will undertake the standard Quitline assessment. A list of those individuals who indicate that they wish to take part in research will be transferred from the Quitline database to the trial research assistants based at Quitline. The research assistants will attempt to make contact with people on the list. Those contacted will be told about the trial and asked if they would like to participate. If the potential participant indicates that they are interested, they are consented and asked for demographic data (age and sex) and checked to see if they meet the inclusion criteria for the trial. For those that do meet the inclusion criteria, further details will be collected about the participant's ethnicity and level of nicotine dependence (as determined by the FTND Questionnaire [6]) and they will be randomised Data from this initial assessment will then be electronically transferred (securely) to the Clinical Trials Research Unit's Oracle database. The research assistant will then collect the following baseline data from each participant over the telephone.

• Demographic information: Socio-economic position, based on income, education and occupation.

• Smoking history: Age when started, number of cigarettes smoked per day, number of years as regular smoker, number of previous unsuccessful attempts to give up in past 12 months and the method used, other types of smoking (pipe, cigar), usual brand/pack size (and how long pack lasts), and type of cigarettes smoked per day (e.g. roll-your-own or factory-made).

• Other smoking related information: Self-rated chances of quitting (measured on a scale of one to five, where one is very low and five is very high), household smoking, smoking in cars.

• Concomitant medication: Information about types of medication currently used will be collected.

• The physical signs and symptoms associated with withdrawal: Measured using the Mood and Physical Symptoms Scale (MPSS) [7]. Additional withdrawal questions will also be asked related to the frequency of disturbed sleep, anxiety, mouth ulcers, cough, impatience, dizziness and increased dreaming [8].

• Alcohol use and abuse: Measured using the Alcohol Use Disorders Identification Test (AUDIT-C), a screening tool that helps to identify people who are hazardous drinkers or have active alcohol use disorders (including alcohol abuse or dependence) [9].

### Outcome measures

#### Primary outcome

The proportion of participants who self-report having stopped smoking at six months after their Quit date. 'Stopped smoking' will be defined as having consumed no nicotine cigarettes (not a single puff) in the previous seven days (seven-day point prevalence).

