**Methods/design:**

This single-blind, randomised trial aims to recruit 1,410 participants through the national telephone-based Quitline service in New Zealand. Participants in the treatment arm will be asked to stop smoking nicotine-containing cigarettes on their chosen Quit day and smoke *ad libitum *nicotine-free (Quest 3) cigarettes for six weeks. At the same time people in this group will be asked to start using NRT patches, gum and/or lozenges (as recommended by Quitline) for eight weeks. Participants in the control arm will be asked to stop smoking completely on their chosen Quit day and start using NRT patches, gum and/or lozenges (as recommended by Quitline) for eight weeks. Data collection will occur at baseline, three and six weeks, and three and six months after Quit day. The primary outcome is the proportion of participants who self-report seven-day point prevalence abstinence at six months since Quit date.

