### Study intervention

Participants will be randomised to a six week intervention of nicotine-free cigarettes (Quest 3) plus eight weeks of usual care (NRT plus behavioural support) *versus *eight weeks of usual care (NRT plus behavioural support).

• Treatment group: Participants allocated to the treatment arm will be asked to stop smoking their normal cigarettes on their chosen Quit day and switch to the nicotine-free cigarettes (Quest 3) couriered to them, then at six weeks to stop smoking the nicotine-free cigarettes (Figure 1). Participants will be told that they should try all the techniques suggested by the Quitline advisors to help them get through the withdrawal period (i.e. drink water, deep breathe, do something else, delay), but if they still feel they must have a cigarette, they should only smoke the nicotine-free cigarettes provided. Participants will also be supported by Quitline in the usual way for eight weeks, with counselling/advice and NRT in the form of a patch, gum and/or lozenge (Figure 1). The Quest 3 cigarettes used in this trial have recently been reformulated by Vector Tobacco Inc and no longer contain genetically modified tobacco. The "new" cigarettes still have a similar nicotine content (1.5 mg per cigarette) and yield (≤ 0.05 mg per cigarette) as the original Quest 3 cigarettes, but the tar content has been reduced from 10mg to 4mg per cigarette. In order to verify the nicotine and tar content of the trial cigarettes, independent verification will be undertaken by Labstat Canada. Specifically, the nicotine content of the unburnt nicotine-free cigarettes will be assessed (including analysis of nicotine alkaloids by gas chromatography and tobacco moisture), as will total particulate matter, water, nicotine, particulate matter (water and nicotine free), carbon monoxide and puff number.

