**Figure 1 F1:**
[figure not shown]
**Schematic of treatment allocation during intervention period**.

• Control group: Participants allocated to the control arm of the trial will be asked to stop smoking completely on their chosen Quit day and will be supported by Quitline in the usual way for eight weeks, with counselling/advice and NRT in the form of a patch, gum and/or lozenge (Figure 1).

Current standard cessation practice at the New Zealand Quitline (as at December 2010) is as follows (other cessation providers in New Zealand do not follow the process outlined here): Quitline issues by post, a Quit Card (with a 90 day expiry) for eight weeks supply of up to three NRT products (patch, gum and/or lozenge) and makes routine support calls by telephone over eight weeks. These support calls are administered by the Quitline advisors as required. Quitting support generally involves an average of three follow-up telephone calls, each lasting about 10-15 minutes. However, if people do not wish to receive support calls, they are not scheduled but callers are advised that they can phone Quitline at any time for support. Participants are advised to take the Quit Card to a pharmacist in exchange for subsidised patches, gum and/or lozenges (NZ$3 per item per four-week course of NRT). The strength of NRT patch, gum, and/or lozenges to be used by each participant is determined by the Quitline advisor (as per their dosage guidelines) as to the degree of each person's nicotine dependency. "Quit day" in this study will refer to the day each participant stops smoking cigarettes containing nicotine.

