#### Secondary outcomes

The following secondary outcome measures will be assessed at three and six weeks after the Quit date in the treatment group only:

• Information related to the use of the nicotine-free cigarettes: Participants will be asked for their views on the use of the nicotine-free cigarettes (including concerns, whether they liked the taste of them, etc), and whether the six weeks use of the cigarettes was adequate. The number of nicotine-free cigarettes and normal cigarettes smoked each week during the intervention period will also be recorded.

• Information related to the use of the NRT: Participants will be asked about their use of NRT during the treatment period.

The following secondary outcome measures will be assessed in all participants at three weeks, six weeks, three months and/or six months after the Quit date:

• The physical signs and symptoms associated with withdrawal at three and six weeks: Measured using the Mood and Physical Symptoms Scale (MPSS) [7]. Additional withdrawal questions will also be asked related to the frequency of disturbed sleep, anxiety, mouth ulcers, cough, impatience, dizziness and increased dreaming [8].

• Self-rated chances of quitting at three and six weeks: Measured on a scale of one to five, where one is very low and five is very high.

• Proportion of participants who have stopped smoking at three weeks, six weeks and three months: Defined as no nicotine cigarettes (not even a puff) in the past seven days.

• Continuous abstinence: Defined as self-report of smoking no more than five nicotine cigarettes from the Quit date, collected at all time points.

• Proportion of participants who have significantly reduced daily smoking level at six months: Defined as reducing consumption by at least 25% (in terms of numbers of cigarettes per day or weight of loose tobacco per day).

• Number of cigarettes currently smoked per day: If the participant is still smoking (all times points). Pack size (and how long pack lasts) if smoking roll-your-owns.

• Cost information: Cost outcomes will include cost per quitter, cost per person reducing their daily cigarette consumption, and cost per Quality Adjusted Life Year of life saved among quitters. The tobacco expenditure savings to individual smokers will also be calculated using data on the daily amount smoked prior to quitting and the price of the particular products smoked.

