#### Treatment effects

Analyses will be undertaken on an intention-to-treat basis, according to a pre-specified statistical analysis plan using SAS version 9.1.3. A per-protocol analysis will also be performed in order to check the robustness of the results. No interim analysis will be undertaken. Chi-squared analyses will be used to compare the proportion quit by treatment group, and incidence rates, relative risks, risk differences, 95% confidence intervals and two-sided p-values will be calculated. Logistic regression analyses will be utilized to adjust for important prognostic factors. Continuous outcome data will be analysed using multiple linear regression modelling. Both the number of cigarettes per day and withdrawal symptoms over time will be compared using analysis of covariance. Pre-specified subgroup analyses using tests for heterogeneity will be undertaken for ethnicity (Māori, non-Māori), age (< 40 years, ≥ 40 years), sex and socioeconomic status (dichotomised as those who left school below Year 12 or with no school qualification, and those who completed Year 12 and above). Analyses will also be undertaken to examine time-to-first-lapse using Kaplan-Meier analysis and self-reported seven-day point prevalence of smoking abstinence at six months in those with complete smoking status data.

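### The abstinence outcomes exempt the trial's own cigarettes, so only the treatment arm can be smoking and still be scored as having stopped

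*Protocol article*

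**What the plan says.** Under Primary outcome, the article names the endpoint as "The proportion of participants who self-report having stopped smoking at six months after their Quit date" and then defines stopping as "having consumed no nicotine cigarettes (not a single puff) in the previous seven days". Under Secondary outcomes, the abstinence measure at three weeks, six weeks and three months uses the same exclusion: "Defined as no nicotine cigarettes (not even a puff) in the past seven days". Continuous abstinence is "Defined as self-report of smoking no more than five nicotine cigarettes from the Quit date, collected at all time points".

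The arms differ in what they may smoke. The abstract has the treatment arm smoking "nicotine-free (Quest 3) cigarettes for six weeks", ad libitum. Study intervention has that arm switch to Quest 3 on Quit day and stop it at six weeks. Controls "will be asked to stop smoking completely on their chosen Quit day". The same section ties Quit day to giving up cigarettes that contain nicotine. Background states that the Quest brand is no longer on sale and can be had only for research.

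On data, Secondary outcomes lists weekly counts of nicotine-free and normal cigarettes for the treatment arm during the intervention period. It also lists cigarettes per day at all time points, for participants who are still smoking.

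**The concern.** The endpoint is presented as stopping smoking, and the objective speaks of long-term quit rates, but the operational rule excludes one class of cigarette only. Because a single arm is supplied with the exempt class, the same wording means different things in the two arms. A treatment participant smoking Quest 3 is recorded as stopped. A control who smokes is in practice smoking a nicotine cigarette and is recorded as not stopped.

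At stake is whether a difference between arms shows more people quitting, or partly reflects people who changed what they smoke. The cost per quitter and the cost per QALY among quitters would inherit the same definition. Outcomes are self-reported, and the callers know the allocation (Blinding), so the scoring rule needs to leave no room for interpretation.

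**Working it through.** **Step 1. Is Quest 3 a nicotine cigarette in this plan?** Quit day is the day the participant gives up nicotine-containing cigarettes. The treatment arm switches to Quest 3 on that same day. The two statements fit together only if Quest 3 is not counted as a nicotine cigarette. The contrast between nicotine-free and normal cigarettes under Secondary outcomes points the same way. The exemption is therefore implied, though the outcome section never states it.

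**Step 2. Who can use the exemption?** Quest 3 is couriered to the treatment arm and is not on sale, so in practice only that arm can.

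**Step 3. Effect at each time point.**

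| Outcome | Treatment participant smoking only Quest 3 | Control who smokes | Status |
|---|---|---|---|
| 3 and 6 weeks, seven-day | abstinent, use is permitted | not abstinent after one puff | certain |
| Continuous, weeks 0-6 | abstinent, even with daily use | fails at the sixth cigarette | certain |
| 3 months, seven-day | abstinent | not abstinent | only if Quest 3 is used after week 6 |
| 6 months, seven-day (primary) | abstinent | not abstinent | only if Quest 3 is used after week 6 |

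**Step 4. Would the data show it?** Quest 3 counts are listed for the intervention period only. Cigarettes per day is asked of those still smoking, and under the plan's definition someone smoking only Quest 3 need not be put in that group. Nothing listed clearly identifies Quest 3 use at three or six months.

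**Step 5. The plan's sample size, for scale.** Sample size states 705 per group, 90% power, a 7.5-point difference and 20% loss, but no control rate. Assume 15% against 22.5%, with mean 0.1875:

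n = [1.96·√(2·0.1875·0.8125) + 1.2816·√(0.15·0.85 + 0.225·0.775)]² / 0.075² = 568 per arm

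568/0.8 = 710 per arm, or 1,420 in total against the stated 1,410. The stated size is consistent with a control rate near 15%, which is why 12-15% is used below. The asymmetry itself does not depend on this.

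**Step 6. Sensitivity at six months.** Let m be the share of the treatment arm smoking only Quest 3 in the seven days before the call. One per cent is 0.01 × 705 ≈ 7 people and adds 1 point to the apparent difference. With no true effect, control rate p and 705 per arm (those lost count as smoking):

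SE = √{[p(1−p) + (p+m)(1−p−m)]/705}, P(significant in favour) = Φ(m/SE − 1.96)

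Example, p = 0.12 and m = 0.01: SE = √[(0.1056 + 0.1131)/705] = 0.0176, and Φ(0.568 − 1.96) = 0.082.

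| m (assumed) | p = 12% | p = 15% |
|---|---|---|
| 0 | 2.5% | 2.5% |
| 1% | 8.2% | 7.5% |
| 2% | 20.0% | 17.5% |
| 3% | 37.8% | 32.9% |

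The documents supply no value for m.

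**The case against.** The strongest reply concerns the primary time point. Participants are asked to stop Quest 3 at six weeks, and it cannot be bought. To be misclassified at six months, someone would have to hold stock for about 20 weeks (26 − 6), smoke it in the final seven days, and take no puff of an ordinary cigarette in that window. The share could be zero, and then the primary comparison is unaffected. This stands. A reader might infer that the primary result is materially biased, but the documents do not show that.

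The early definition can also be defended. Quest 3 is the assigned treatment at three and six weeks, the strategy targets nicotine dependence, and the wording is openly stated. Scoring permitted treatment as relapse would bring its own difficulty of interpretation. This stands as a reason to report both versions rather than replace one. It does not justify calling the result stopped smoking.

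Four stronger readings are tempting and not supported:

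- Quest 3 is said to "still have a similar nicotine content (1.5 mg per cigarette"), so it might be called a nicotine cigarette, which would turn treatment-arm participants who smoke it into failures at three and six weeks. That conflicts with the Quit-day definition and the same-day switch. One clarifying clause settles it.
- The analysis of "time-to-first-lapse using Kaplan-Meier analysis" might be thought to carry the same asymmetry. The article does not define a lapse, and may leave that to the analysis plan.
- Six-month continuous abstinence might be said mainly to measure switching. It also requires about 20 weeks with almost no nicotine cigarettes after Quest 3 is due to end.
- The early data might be thought inadequate. The treatment-arm counts for weeks three and six are already collected.

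**Conclusion.** The point holds as a flaw in the outcome definition. Its effect is certain for the three- and six-week abstinence outcomes and for the first six weeks of continuous abstinence. There the distortion can be as large as the share of the treatment arm that smokes Quest 3 and would otherwise meet the definition.

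For the primary outcome the effect is conditional: 1 point of apparent difference per 1% of the arm still smoking only Quest 3, against a 7.5-point target. One point would raise the chance of a false favourable result from 2.5% to about 8%. That figure rests on three assumptions: no true effect, a control rate of 12-15%, and a residual share of 1%. The true share may be smaller or nil. What makes the point worth acting on is that the plan has no rule for scoring late Quest 3 use and no listed item that would clearly reveal it, so the size could not be settled afterwards.

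**What to change.** 1. Define the six-month primary outcome and the three-month outcome, in both arms, as no cigarette of any kind, trial cigarettes included, in the past seven days. Keep the present definition as a labelled sensitivity analysis.
2. Ask about trial-cigarette use at the three- and six-month calls, covering both the past seven days and the time since week six.
3. Label the three- and six-week outcomes as abstinence from nicotine cigarettes, state that Quest 3 is exempt there, and report abstinence from all cigarettes beside them, using the treatment-arm counts already collected.
4. Add continuous abstinence from all cigarettes counted from week six, beside the present measure from Quit date.

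The cost is some wording and one extra question at two calls. The treatment-arm quit rate may come out slightly lower. If, for example, 1 of the 7.5 points reflected Quest 3 use, power at a 15% control rate with 564 evaluable per arm (705 × 0.8) would fall from 89.8% to 80.8%. The change should be fixed before the allocation code is broken.

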#### Secondary outcomes

The following secondary outcome measures will be assessed at three and six weeks after the Quit date in the treatment group only:

• Information related to the use of the nicotine-free cigarettes: Participants will be asked for their views on the use of the nicotine-free cigarettes (including concerns, whether they liked the taste of them, etc), and whether the six weeks use of the cigarettes was adequate. The number of nicotine-free cigarettes and normal cigarettes smoked each week during the intervention period will also be recorded.

• Information related to the use of the NRT: Participants will be asked about their use of NRT during the treatment period.

The following secondary outcome measures will be assessed in all participants at three weeks, six weeks, three months and/or six months after the Quit date:

• The physical signs and symptoms associated with withdrawal at three and six weeks: Measured using the Mood and Physical Symptoms Scale (MPSS) [7]. Additional withdrawal questions will also be asked related to the frequency of disturbed sleep, anxiety, mouth ulcers, cough, impatience, dizziness and increased dreaming [8].

• Self-rated chances of quitting at three and six weeks: Measured on a scale of one to five, where one is very low and five is very high.

• Proportion of participants who have stopped smoking at three weeks, six weeks and three months: Defined as no nicotine cigarettes (not even a puff) in the past seven days.

• Continuous abstinence: Defined as self-report of smoking no more than five nicotine cigarettes from the Quit date, collected at all time points.

• Proportion of participants who have significantly reduced daily smoking level at six months: Defined as reducing consumption by at least 25% (in terms of numbers of cigarettes per day or weight of loose tobacco per day).

• Number of cigarettes currently smoked per day: If the participant is still smoking (all times points). Pack size (and how long pack lasts) if smoking roll-your-owns.

• Cost information: Cost outcomes will include cost per quitter, cost per person reducing their daily cigarette consumption, and cost per Quality Adjusted Life Year of life saved among quitters. The tobacco expenditure savings to individual smokers will also be calculated using data on the daily amount smoked prior to quitting and the price of the particular products smoked.

• Use of NRT: Participants will be asked about continued use of any NRT (including type, dosage, flavour, and frequency of use) at all time points.

• Use of non-NRT methods of cessation at six months: Participants will be asked about their use of non-NRT methods of cessation such as buproprion, clonidine, nortriptyline, varenicline, acupuncture etc.

• Alcohol use and abuse at six months: Measured using the AUDIT-C [9].

• Serious adverse events: Information regarding any serious adverse events and whether they are related to treatment will be collected at all time points.

• Concomitant medication: collected at all time points

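### Cigarettes per day is defined only for participants still smoking, yet it is compared between arms by analysis of covariance; as written, this is not a randomised comparison

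*Protocol article*

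**What the plan says.** In the protocol article, Secondary outcomes, one group of measures "will be assessed in all participants at three weeks, six weeks, three months and/or six months after the Quit date". Within that group stands "Number of cigarettes currently smoked per day: If the participant is still smoking (all times points"). The Treatment effects section then states: "Both the number of cigarettes per day and withdrawal symptoms over time will be compared using analysis of covariance". It opens with the general rule "Analyses will be undertaken on an intention-to-treat basis". Nowhere does the article assign a value to a participant who has stopped.

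On which cigarettes count:
- Under Primary outcome, having stopped "will be defined as having consumed no nicotine cigarettes (not a single puff) in the previous seven days".
- Under Study intervention, Quit day "in this study will refer to the day each participant stops smoking cigarettes containing nicotine".
- The point-prevalence and continuous-abstinence items under Secondary outcomes also specify nicotine cigarettes. The cigarettes-per-day item does not.
- For the treatment group only, "The number of nicotine-free cigarettes and normal cigarettes smoked each week during the intervention period will also be recorded".
- Controls "will be asked to stop smoking completely on their chosen Quit day and will be supported by Quitline in the usual way".

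Daily consumption before quitting is collected under Baseline assessments.

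**The concern.** A mean taken only over people still smoking compares two groups that the treatment itself has helped to form. If the intervention works, some people who would have smoked under control drop out of the treatment mean. If they would have been light smokers, the treatment mean rises; if heavy smokers, it falls. Neither movement is an effect on anyone's consumption.

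The intention-to-treat sentence does not settle this. It keeps people in the arm to which they were randomised, but it supplies no value for people whom the outcome definition leaves out. The restriction applies at every follow-up.

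A second, smaller gap exists only at weeks three and six, while the treatment arm may be using trial cigarettes. If still smoking means nicotine cigarettes, a person smoking only trial cigarettes has no value. If it means any cigarette, such people enter the mean in one arm only.

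At stake is the reading of one secondary result: whether the intervention changes how much people smoke.

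**Working it through.** The article gives no figure for this outcome, so there is none to reproduce. From the Sample size section come 705 per arm and 20% loss. Everything else below is assumed, for illustration.

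**1. How many people have no value.** Applying the 20% loss at week six, 705 × 0.80 = 564 per arm, or 1,128 in all. Assume nicotine abstinence of 40% (treatment) and 30% (control).
- Treatment: 564 × 0.40 = 226. Control: 564 × 0.30 = 169. Together 395/1,128 = 35%.
- At 30% v 20%: 169 + 113 = 282, or 25%. At 50% v 30%: 282 + 169 = 451, or 40%.

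**2. What selection alone does.** Keep 40% v 30%. Then 30% quit in either arm, 10% quit only on treatment (they would smoke *c* a day as controls), and 60% smoke in either arm (mean *m*, unchanged by treatment). Fix the control mean among smokers at 10 a day, which is half of an assumed baseline of 20:

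(0.1*c* + 0.6*m*)/0.7 = 10, so *m* = (7 − 0.1*c*)/0.6.

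With zeros for those who stopped, the mean in everyone followed is 0.6*m* on treatment and 0.7 × 10 = 7.0 on control.

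| *c* | Still smoking, treatment v control | Difference | All followed, treatment v control | Difference |
|---|---|---|---|---|
| 4 | 11.0 v 10.0 | +1.0 | 6.6 v 7.0 | −0.4 |
| 6 | 10.7 v 10.0 | +0.7 | 6.4 v 7.0 | −0.6 |
| 10 | 10.0 v 10.0 | 0.0 | 6.0 v 7.0 | −1.0 |
| 14 | 9.3 v 10.0 | −0.7 | 5.6 v 7.0 | −1.4 |

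Treatment lowers consumption in every row, yet the still-smoking difference is positive, zero or negative according to *c*.

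**3. A second set of assumptions.** Let 75% of controls and 67.5% of the treatment arm smoke, with persistent smokers at 14 a day in both arms. If the extra 7.5% would have smoked 6 a day, the control mean among smokers is (0.675 × 14 + 0.075 × 6)/0.75 = 13.2, against 14.0 on treatment (+0.8). In everyone, control is 0.75 × 13.2 = 9.90 and treatment 0.675 × 14 = 9.45 (−0.45). At 10 a day the two differences are +0.4 and −0.75; at 14 a day they are 0.0 and −1.05.

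**4. Which cigarettes count.** Return to 40% v 30% with continuing smokers at 10 a day in both arms. On the nicotine reading the still-smoking means are 10 v 10. Now let a quarter of treatment-arm abstainers use 2 trial cigarettes a day. On the any-cigarette reading the treatment mean is (0.6 × 10 + 0.4 × 0.25 × 2)/(0.6 + 0.4 × 0.25) = 6.2/0.7 = 8.9, against 10. The choice of reading alone moves the difference from 0 to −1.1.

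**The case against.** The strongest reply is that the condition is interview routing and not an analysis population. The next sentence of the same item asks about pack size only if the person smokes roll-your-owns, which is plainly a skip instruction. The item is listed among outcomes assessed in all participants, the analysis section puts no smokers-only limit on the analysis of covariance, and that section names its restriction where it wants one (the complete-data analysis of abstinence). Someone with no nicotine cigarette in seven days has a known count of zero, and such coding could sit in the analysis plan, which is not shown.

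This is plausible, and it is the main reason to rate the point low. It does not remove it. The article is not silent: it states a condition, names a between-arm comparison, and nowhere restores the zeros. Followed literally, the comparison is among smokers only.

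Adjusting for baseline consumption would help only in part. It removes selection explained by the baseline count, not selection by other traits, and it still leaves out those who stopped.

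On trial cigarettes, the Quit day definition, the primary outcome and the abstinence items all point to nicotine cigarettes as the natural reading. The gap is one of wording.

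A reader might also infer that the treatment arm has only weekly counts and controls only daily ones. The text does not support that: the per-day item covers both arms, and the weekly counts are an addition for the treatment group.

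**Conclusion.** The point stands as a minor one. As written, the comparison of cigarettes per day conditions on a post-randomisation state that is itself a trial outcome, at all follow-ups. It would omit about a quarter to two fifths of those followed under the abstinence rates assumed, and it can differ from the all-participant effect in size or sign. The direction cannot be known in advance; the illustrations rest on assumed abstinence, baseline and reduction figures and are unadjusted means.

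Stronger conclusions are tempting but are not supported:
- That the result will favour, or disfavour, the intervention. The still-smoking difference takes either sign under reasonable inputs.
- That the plan misjudges total cigarettes or smoke exposure at weeks three and six. The article's objective is quitting, it sets trial cigarettes as a fallback, and their extent of use is unknown. A total-cigarettes comparison is a different question, not an omission.
- That the main result is at risk. The six-month primary outcome does not use this measure, and abstinence in all participants at the earlier visits is planned separately.

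**What to change.** **Secondary outcomes.** Replace the condition on still smoking with: nicotine cigarettes per day at every time point, recorded as zero for those who have stopped.

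**Treatment effects.** State that this outcome is compared in all randomised participants with follow-up, by analysis of covariance adjusted for baseline cigarettes per day, with robust standard errors because of the zeros. Keep the mean among those still smoking as descriptive only. Report nicotine-free cigarettes separately, from the treatment-arm counts already planned. A comparison of total cigarettes of any type at weeks three and six is optional.

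**Cost.** A clause in each of two sections and a coding rule. The baseline count, the abstinence status and the per-day item are already planned in both arms; the follow-up question need only specify nicotine cigarettes. The all-participant mean combines quitting with cutting down, so it should be shown beside the abstinence proportions and the descriptive mean.
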